## Abstract

**Introduction:**

The classical pathway for the therapy of low- to intermediate-risk localized prostate cancer is radical prostatectomy or radiation therapy, which has shown a high incidence of complications, including erectile dysfunction, urinary incontinence, and bowel injury. An alternative pathway is to perform an ablation by some energy to the localized lesion, known as focal therapy. High-frequency irreversible electroporation (H-FIRE) is nonthermal energy that can be used in cancer ablation to deliver pulsed high-voltage but low-energy electric current to the cell membrane and to invoke cell death. An H-FIRE pathway has been reported to be tissue-selective, which leads to fewer side effects.

**Methods and Analysis:**

This is a multicenter and single-arm objective performance criteria (OPC) study, in which all men with localized prostate cancer are allocated to H-FIRE ablation. This trial will assess the efficacy and safety of the H-FIRE ablation for prostate cancer. Efficacy will be assessed by prostate biopsy 6 months after treatment while safety will be assessed by adverse event reports and questionnaires. The main inclusion criteria are moderate to low-risk prostate cancer in NCCN risk classification and had no previous therapy for prostate cancer. A sample size of 110 participants is required. The primary objective is to determine whether the detection rate of clinically significant cancer by prostate biopsy is less than 20% after the H-FIRE ablation.

**Ethics and Dissemination:**

This study has obtained ethical approval by the ethics committee of all participating centers. The results of the study will be submitted for dissemination and publication in peer-reviewed journals.

**Conclusions:**

This multicenter single-arm objective performance criteria trial will evaluate the efficacy and safety of the use of high-frequency irreversible electroporation in treating prostate cancer.

**Strengths and Limitations of This Study:**

A comprehensive evaluation of imaging and histopathology is used to determine the effect of treatment. Questionnaires were used to assess the treatment side effects. Multicenter and pragmatic designs capacitate higher generalizability. A limitation of this trial is that the prostate biopsy as an endpoint may not be as accurate as of the specimen from prostate prostatectomy. Another limitation is the 6-month follow-up time, making this trial challenging to come to firm conclusions regarding the efficacy and safety of IRE in the long term.

**Clinical Trial Registration:**

ClinicalTrials.gov, NCT03838432

## Introduction

Prostate cancer is the second most prevalent male cancer and the fifth most common cancer death for men worldwide, which accounted for 13.5% of cancer cases and 6.7% of cancer deaths (1). The traditional pathway for the therapy of low to intermediate-risk prostate cancer, radical prostatectomy, or radiation therapy aims to eliminate the whole gland rather than the localized cancer tissue. Although the treatment is efficacy, it may damage the neurovascular bundles, bladder neck, and rectum, which will lead to complications of erectile dysfunction, urinary incontinence, and bowel injury. These complications and side effects seriously reduce the quality of life. Another pathway in treating low-risk disease is active surveillance, also to prove the efficacy and safety (2). However, there are several barriers, such as patient education or anxiety that were challenging for the continuation of active surveillance (3). Also, it will bring psychosocial and financial burdens for patients who were under active surveillance for a long period of time.

To maintain the efficacy and avoid the side effect of the current pathway, a selective pathway between active surveillance and radical treatment is emerging, which is known as focal therapy. This pathway aims to destroy the focal cancer lesions and preserve the surrounding benign tissue. There are various energy sources that have been used for focal therapy. The prevalent type of energy is thermal energy, including high-intensity focused ultrasound (HIFU), laser, and cryotherapy, which lead to lethal effects by generating extreme temperatures (4). Another novel nonthermal technique for ablation is irreversible electroporation (IRE), which delivers pulsed high voltage, but the low-energy direct electric current through the specialized electrode needles generates a short and intense electrical field to the cell membrane, thereby invoking cell death (5). The potential advantage of IRE seems to be tissue-selective with little damage to the connective tissue structure (6). That is to say, some vital structures like blood vessels or nerves may be reserved after an ablation procedure (6, 7). The traditional IRE applies 80 to 120 unipolar pulses with a pulse of 50 to 100 μs and an electric field >1,000 V/cm. However, this typical IRE protocol may evoke muscle contraction during the procedure, leading to pain for the patients and causing displacement of the electrode needles. Recently, a new type of IRE technique called high-frequency IRE (H-FIRE) has emerged (8). H-FIRE utilizes a set of bipolar pulse burst. Each burst consists of some individual pulses range from 0.5 to 10 μs, and the total time of a single burst is up to 100 μs. Some animal experiments had verified the efficacy of H-FIRE in tumor killing and reduction in muscle contraction. We also preliminarily confirmed that H-FIRE could preserve the urethra and major vasculature in the prostate in the human pilot trial (9).

This multicenter trial aims to evaluate the efficacy and safety of H-FIRE ablation for men with localized prostate cancer. The primary objective is to determine if the clinically significant cancer is detected by less than 20% by prostate biopsy after the ablation.

### Outcomes

The primary outcome is the detection rate of clinically significant prostate cancer, defined as any biopsy core with a Gleason score of 3 + 4 or more, or a Gleason score of 3 + 3 plus maximum cancer core length at >3 mm, or an increase from the original cancer burden in the ablation area 6 months post H-FIRE.

The main secondary objectives are as follows:

To assess the proportion of men with serum PSA level at >2 ng/ml over the nadir in 6 months post H-FIRE;To assess the adverse events according to Common Terminology Criteria for Adverse Events (CTCAE) at any time post H-FIRE;To assess the proportion of men using pads preoperative and 1 months, 3 months, and 6 months post H-FIRE;To assess the urinary symptoms by questionnaire of International Prostate Symptom Score (IPSS) scoring preoperative and 1 months, 3 months, and 6 months post H-FIRE;To assess the erectile symptoms by International Index of Erectile Function (IIEF-5) scoring preoperative and 1 months, 3 months, and 6 months post H-FIRE; andTo assess the time of urinary catheter retention.

### Trial Design

This prospective, multicenter and single-arm objective performance criteria (OPC) trial will take place at four academic medical centers in China: Changhai Hospital, Shanghai; Renji Hospital, Shanghai; Peking Union Medical College Hospital, Beijing; and Changzheng Hospital, Shanghai. The main objective of this study is to assess the efficacy and safety of high-frequency irreversible electroporation (H-FIRE) for the ablation of prostate cancer. All participants who meet the entry criteria will undergo H-FIRE and subsequently receive prostate biopsy 6 months later (**Figure 1**). This trial is approved by the committee for medical and health ethics of all centers and registered on ClinicalTrials.gov (NCT03838432).

**Figure 1 f1:**
[figure not shown]
Trial flowchart.

## Methods and Analysis

### Patient Population

Patients with a new diagnosis of low-risk or intermediate-risk prostate cancer in NCCN risk classification and who had no previous therapy for prostate cancer will be seen as qualifying for registration in the trial if they can meet all inclusion criteria and had no exclusion criteria. The main criteria include men with elevated serum PSA less than 20 ng/ml, suspected stage less than or equal to T2c, and biopsy Gleason score less than or equal to 4 + 3. The details of inclusion and exclusion criteria are shown in **Table 1**. All eligible patients will be informed in detail; only those who sign the consent will enter the trial. Patients who are ineligible or do not want to participate in this trial will be returned to the regular clinical pathway, active surveillance, or radical treatment.

**Table 1 T1:** Patients inclusion and exclusion criteria.

Inclusion criteria
Age range from 40 to 85 years old
Prostate cancer must be detected by template-guided mapping biopsy or targeted plus template-guided mapping biopsy
Serum PSA < 20 ng/ml
Suspected stage ≤ T2c (organ confined)
Biopsy Gleason score ≤ 4 + 3
No prostatic calculus or prostatic calculus ≤ 5 mm
Fully understand the clinical trial protocol and sign the informed consent
**Exclusion criteria**
Previous history of radical prostatectomy, hormonal therapy, or radiotherapy
Previous surgery within 3 months
Long-term medication with anticoagulant or stop taking anticoagulant less than 1 months
Not fit for anesthesia or surgery
With cardiac pacemaker and/or with metal implants which are located in the range from the first lumbar vertebra (L1) to the middle of femurs.
Previous history of epilepsy
Any other malignant tumor or HIV

### Baseline Characteristics

Blood and urine samples will be collected before IRE for a routine examination. Performance status (Eastern Cooperative Oncology Group, ECOG) will be used to evaluate the general health status and tolerance to treatment. Also, the questionnaire of International Prostate Symptom Score (I-PSS) will be used to assess the baseline urinary symptoms, and the International Index of Erectile Function (IIEF-5) will be used to evaluate the baseline erectile symptoms (10).

### Multi-Parametric Magnetic Resonance Imaging

All participants who sign the informed consent will undergo a 3.0-T multiparametric magnetic resonance imaging (mpMRI) three times: within 1 month pre H-FIRE, 1 month post H-FIRE, and 6 months post H-FIRE. The sequences of examination mainly included T2-weighted imaging (T2WI), diffusion-weighted imaging (DWI), and dynamic contrast-enhanced imaging. Images will be evaluated and scored by expert radiologists according to the Prostate Imaging Reporting and Data System (PI-RADS) (11). The MRI before H-FIRE aims to be performed for localizing the tumor lesions and for scheming the ablation region or range. After the MRI examination, patients will undergo a 12–20-region template-guided prostate biopsy combined with targeted biopsy (for MRI-positive patients) to locate the lesions of the prostate (12, 13). The coordinate of each biopsy core will be marked down. Hence, we can target the focal lesion precisely according to the coordinate. The follow-up MRI will reevaluate the prostate, both the ablation area and untreated area, and provide the evidence for the prostate biopsy 6 months post H-FIRE.

### Clinical Pathway

Participants will be hospitalized 1 day before the IRE. The IRE will be performed *via* the perineum with the guidance of ultrasound under general anesthesia. A Foley catheter and prophylactic antibiotics will be given to patients after the procedure. All participants will be scheduled to be dismissed the following day after IRE. After discharge, the patient will take 1 week of antibiotics, alpha1-adrenoceptor antagonists, and painkillers. The catheter will be retained for 3 to 14 days according to the ablation range and area and will be withdrawn at the outpatient clinic. If the patient is unable to void after removing the catheter, he will be given another Foley catheter for 1 more week.

### Follow-Up and Study Endpoint

MRI will be organized 1 and 6 months after IRE, and serum PSA measurement will be organized 1, 3, and 6 months. Patients will be scheduled to respond the questionnaires including I-PSS, IIEF-5, and pad usage records at 1, 3, and 6 months. At 6 months, all participants will receive a prostate biopsy to get the sample for pathological evaluation. The details and timeframe of follow-up are shown in **Table 2**. This trial will discontinue due to the following: (1) more than 20% of the total number of cases deviated from the protocol; (2) the number of dropout cases exceeds 20% of the total number of designed cases; (3) the severity and frequency of serious adverse events that occurred tended to exceed those reported in local treatment literature; and (4) the severity and frequency of instrument defects and faults exceed the acceptable risk.

**Table 2 T2:** Participant timeline in the study.

	Contact with patient					
	Vist 1	Vist 2	Vist 3	Vist 4	Vist 5	Vist 6
	Pre H-FIRE	H-FIRE	1-week post H-FIRE	1-month post H-FIRE	3-month post H-FIRE	6-month post H-FIRE
Time	-30~0 days	0	7~10 days	4~6 weeks	12~14 weeks	6~7 months
Consent	×					
Screening	×					
Baseline characteristic	×					
PSA	×			×	×	×
Routine blood test	×		×	×	×	×
Routine urine test	×		×	×	×	×
Blood biochemistry test	×		×	×	×	×
ECT	×					
Performance status	×					
MRI	×		×			×
Prostate biopsy	×					×
Pathological assessment	×					×
NCCN risk assessment	×					
Clinical stage assessment	×					
Pad usage record	×			×	×	×
IIEF–5 scoring questionnaire	×			×	×	×
IPSS scoring questionnaire	×			×	×	×
Urinary catheter removed			×			
Withdrawal	Complete as required at any time following registration					
SAE	Complete as required at any time following registration					

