### Calculation of Sample Size

The detection rate of significant cancer after focal therapy is clinically acceptable to be 20% (14). The previous data from the Changhai hospital showed the detection rate of significant cancer after ablation to be 9%.

For the single arm OPC hypothesis, employing 80% power, 2.5% one-sided α, and a 95% two-sided confidence interval, 87 men will be required. Assuming there is a 20% withdrawal/loss in follow-up, 110 participants are expected to be enrolled.

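### The mandatory dropout stop is set at the same 20% loss that the sample size plans for, so a trial losing men at the planned rate has about a 44% chance of meeting it

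*Protocol article*

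**What the plan says.** The Follow-Up and Study Endpoint section introduces four grounds for ending the trial with the words "This trial will discontinue due to the following". The second is that "the number of dropout cases exceeds 20% of the total number of designed cases". The wording is mandatory. The article describes no review step, and no exception for the case where enough men remain for the primary analysis.

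The Calculation of Sample Size section states that, "employing 80% power, 2.5% one-sided α, and a 95% two-sided confidence interval, 87 men will be required". It continues: "Assuming there is a 20% withdrawal/loss in follow-up, 110 participants are expected to be enrolled". The abstract repeats the total: "A sample size of 110 participants is required".

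The remaining grounds are protocol deviations (the first), serious adverse events (the third) and device faults (the fourth).

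**The concern.** A dropout allowance in a sample size states how much loss the trial can absorb and still answer its question. A stopping limit on dropout should therefore lie clearly beyond that allowance. Here the two coincide. One section enrols extra men to cover a 20% loss, and another ends the trial as soon as the loss passes 20%. Ordinary chance variation around the planned rate is then enough to end the trial for a reason that is neither safety nor device performance.

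At stake is the primary result, the 6-month biopsy detection rate in men who have already been treated. Stopping on a dropout count could leave that result incomplete when the evidence lost to dropout itself is small.

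**Working it through.** **Inputs.** All are from the protocol article.
- Acceptable detection rate p0 = 20%, expected rate p1 = 9%, 80% power, one-sided α 2.5%, 87 men required, 20% loss, 110 enrolled (Calculation of Sample Size).
- Stop when dropouts exceed 20% of designed cases (Follow-Up and Study Endpoint).
- Designed cases are taken as 110, the stated sample size.

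**1. Reproduce the plan's figures.** One-sample proportion, normal approximation, with the null variance for α and the alternative variance for power:

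n = [(1.960 × √(0.20 × 0.80) + 0.842 × √(0.09 × 0.91)) / (0.20 − 0.09)]² = [(0.784 + 0.241) / 0.11]² = 86.8, rounded up to 87.

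Inflation for loss: 87 / 0.80 = 108.75, so 109. The plan's 110 is a small rounding up. The sample size is not in error.

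**2. Locate the trigger.** 0.20 × 110 = 22. Exceeding 22 means the 23rd dropout. At that moment 110 − 23 = 87 men have not dropped out.

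**3. Chance of reaching the trigger.** Let X be the number of dropouts, X ~ Binomial(110, d), with independent dropouts and full enrolment. At d = 0.20 the mean is 22 and the standard deviation is √(110 × 0.20 × 0.80) = 4.2, so the trigger lies about a quarter of a standard deviation above the mean.

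| True loss d | P(X ≥ 23) |
|---|---|
| 10% | 0.0005 |
| 15% | 0.059 |
| 18% | 0.247 |
| 20% (planned) | 0.443 |
| 22% | 0.645 |
| 25% | 0.866 |

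If designed cases meant the 87 required men, the limit would be 0.20 × 87 = 17.4. The 18th dropout would then trigger the rule, and the probability at 20% loss would be 0.859.

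**4. Split the 44% by how many men would remain at the end of follow-up.**
- P(X = 23) = 0.091: exactly 87 remain.
- P(X ≥ 24) = 0.353: fewer than 87 remain.

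So in 0.353 / 0.443 = 80% of the trials that meet the rule, the final number would be below 87 if they were allowed to run on.

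**5. What a shortfall costs.** With the approximation from step 1, power = Φ[(0.11 × √n − 0.784) / 0.286].
- n = 87: Φ(0.846) = 80.1%.
- n = 80: Φ(0.698) = 75.8%.

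At a true loss of 20%, 94% of the trials that meet the rule have at most 30 dropouts, so at least 80 men remain. The loss of power in those trials is therefore at most about 4 points.

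**The case against.** **The 20% may be a ceiling.** The article does not say whether its 20% is an expected rate or a cautious upper limit. Read as a ceiling, a stop when it is exceeded is coherent, and the risk at lower true rates is modest (6% at 15%) or negligible (0.05% at 10%). This stands as a limit on the size of the problem. It does not remove it, because 20% is the only rate the article gives.

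**The stop may coincide with a real shortfall.** A reader might infer that the trial has a 44% chance of being stopped with all 87 required men evaluable. The figures do not support that. When the rule is first met, 87 men have not dropped out, but those still in follow-up have not had the 6-month biopsy, and some may yet drop out. Counted to the end, exactly 87 remain in about 9% of trials. In the other 35% the required number would be missed anyway, usually by a few men and at a small cost in power. Nor does the article give accrual or dropout timing, or say that data already collected would go unanalysed. A stop late in the trial, or complete loss of the primary result, cannot be asserted.

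**The deviation rule.** A reader might extend the point to the first ground, that "more than 20% of the total number of cases deviated from the protocol", since it also uses 20% and does not say which deviations count. That does not follow. Only the dropout rule matches the loss assumption. Which deviations count is a definition that an article can leave to the full protocol. Any probability for that rule would need a deviation rate per visit, which the article does not give.

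**Conclusion.** The point holds for the dropout rule alone. A mandatory stop unrelated to safety is placed at the loss the sample size is built to absorb. If the true loss equals the planned 20%, the chance of meeting the rule is about 44%, falling to 25% at 18% and 6% at 15%. These figures assume independent dropouts, full enrolment and designed cases equal to 110.

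The sample size itself reproduces, and neither the endpoint nor the inference is invalidated. This should be fixed, but it is not a fatal flaw.

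**What to change.** Reconcile the two sections in one of two ways:
- turn the dropout rule into a trigger for review, in which the number of men still able to provide a 6-month biopsy is weighed before any decision; or
- tie the rule to the projected number of evaluable men compared with the number required.

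State whether designed cases means 110 or 87. Leave the serious adverse event and device rules as they are.

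The cost is a short protocol amendment. The downside is that a trial with somewhat more loss than planned would continue with slightly lower precision, about 4 points of power at 80 men.

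### Discontinuation rule (2) closes the trial at the same 20% loss that the sample size already allows for, so a trial running to plan has about a 44% chance of mandatory closure

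*Protocol article*

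**What the plan says.** Three places in the Protocol article bear on this.

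- **Follow-Up and Study Endpoint.** The list of closure conditions opens with "This trial will discontinue due to the following". Condition (2) is met when "the number of dropout cases exceeds 20% of the total number of designed cases". Conditions (3) and (4) deal separately with serious adverse events and device faults.
- **Calculation of Sample Size.** Against a performance criterion of 20% and an expected detection rate of 9%, the article states: "employing 80% power, 2.5% one-sided α, and a 95% two-sided confidence interval, 87 men will be required". It continues: "Assuming there is a 20% withdrawal/loss in follow-up, 110 participants are expected to be enrolled".
- **Abstract, Methods and Analysis.** The design size is repeated: "A sample size of 110 participants is required".

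Nothing in the article makes condition (2) subject to review or links it to the 87 evaluable men.

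**The concern.** The same 20% is given two incompatible roles. In the sample size section it is ordinary loss, paid for in advance by enrolling 110 instead of 87. In the follow-up section it is the point beyond which the trial must close. A limit set at the expected value of a random count will be crossed often by chance alone, even when retention is what the plan assumed.

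The primary answer is at stake. Condition (2) is not a safety rule, since safety and device faults have their own conditions. It protects the amount of data, but it does so by ending data collection. The stated 80% power also takes no account of the chance that the trial is closed first.

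**Working it through.** **Inputs.** Criterion p0 = 0.20, expected rate p1 = 0.09, one-sided α = 0.025, power 80%, required 87, allowed loss 20%, enrolled 110 (all from the sample size section); closure when dropouts exceed 20% of designed cases (follow-up section). I read designed cases as the 110 to be enrolled.

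**1. The plan's own figures.** One-sample proportion, normal approximation with null and alternative variances:

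n = [(1.960·√(0.20·0.80) + 0.842·√(0.09·0.91)) / (0.20 − 0.09)]² = 86.8, so 87. This reproduces the plan.

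Dividing by the retained fraction gives 87/0.80 = 108.75, so 109, which the plan rounds to 110. Enrolment therefore already covers the 20% loss.

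**2. When the rule fires.** 0.20 × 110 = 22. More than 22 means 23, and 110 − 23 = 87.

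**3. How often it fires.** With X dropouts distributed as binomial(110, d):

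| True loss d | P(X ≥ 23), rule fires | P(X ≥ 24), fewer than 87 remain |
|---|---|---|
| 15% | 5.9% | 3.5% |
| 17.5% | 20.5% | 14.4% |
| 20% (planned) | 44.3% | 35.3% |
| 25% | 86.6% | 81.0% |

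At the planned loss, P(X = 23) = 44.3% − 35.3%, about 9.1% before rounding. That is the only count at which the rule fires while 87 men can still be evaluable.

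**4. What the extra dropouts cost in power at a true rate of 9%.**

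- Normal approximation: power = Φ[(0.11·√n − 1.960·0.40)/√0.0819]. This gives 80.1% at n = 87 and 75.8% at n = 80.
- Exact binomial test at one-sided 2.5%: with 87 men, at most 9 positives are allowed and power is 74.4%. With 80 men, at most 8 are allowed and power is 70.8%.

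The two methods should not be mixed. Like for like, losing seven more men than planned costs about 4 percentage points of power.

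**5. Precision.** At an observed 9%, the approximate 95% half-width is 1.96·√(0.0819/n). That is 6.0 percentage points at 87 and 6.3 at 80.

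**6. Other reading.** If designed cases meant the 87, the rule would fire at 18 dropouts, with 110 − 18 = 92 men remaining. The chance at a 20% loss would be 86%. That reading makes the conflict worse.

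**The case against.** The strongest reply is that 20% is only an assumption, and a loss allowance may be deliberately cautious. If the real loss is 15%, the rule fires in about 6% of trials. This stands: 44% applies only if the true loss is 20%. But 20% is the plan's own figure, and a closure limit should tolerate the loss that the plan says it expects.

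A second reply is that the rule does not bias the estimate, change the hypothesis or inflate the type I error. That also stands, and it limits the severity.

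Some stronger readings are tempting, but the article does not support them:

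- **That the 44% is the chance of stopping a trial that still has its required sample.** It is not. Only about 9 of the 44 points are at exactly 23 dropouts. In the other 35, fewer than 87 men remain.
- **That most men would already have been treated, so stopping protects nobody.** The article gives no accrual rate, and the participant timeline allows withdrawal at any time after registration, which includes before ablation.
- **That closure throws the collected data away.** The article does not say that biopsies already due would be cancelled or that the data would go unanalysed.
- **That a man who skips the 6-month biopsy escapes the dropout count.** The article does not define dropout, and a condensed article may leave that definition to the full protocol.

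**Conclusion.** The conflict is real. Condition (2) mandates closure at the loss the sample size section has already budgeted for, and no text softens it. At the planned 20% loss the chance of closure is about 44%, falling to 20% at a 17.5% loss and 6% at 15%. In most of those cases the 87 target is narrowly or clearly missed, but a modest shortfall costs only a few points of power, and mandatory closure is a disproportionate answer to it.

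The figures assume that all 110 men are enrolled, that dropouts are independent with a common risk, and that designed cases means 110. That 87 are still evaluable at 23 dropouts further assumes that every man who stays has his 6-month biopsy. Severity: should be fixed. The rule puts completion of the trial at risk, not the validity of its estimate.

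**What to change.** Reconcile the follow-up section with the sample size section by changing condition (2) from automatic closure to a data-sufficiency trigger. For example: *if the number of men who can still provide an evaluable 6-month biopsy falls below 87, the sponsor reviews retention; follow-up continues and the primary analysis is done with its achieved precision stated.*

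This trigger is reached at 24 dropouts, only one man later than the present limit. The gain comes from replacing closure with review, not from moving the threshold.

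If an automatic limit is kept, set it clearly above the planned loss and justify it by the precision that would remain. As an illustration only, a limit of more than 33 of 110 (30%) has a 0.4% chance of firing at a true 20% loss, but it tolerates as few as 77 evaluable men. The approximate half-width at an observed 9% would then be 6.4 percentage points.

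Leave conditions (3) and (4) on safety and device faults untouched.

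The cost is one sentence, with no added patients or procedures. The downside is that the trial may finish with somewhat fewer than 87 evaluable men and a slightly wider confidence interval.
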